### Study endpoints

The primary endpoint measure is to detect differences between MS (active treatment) and FS (control) greater than or equal to 0.10-point change from the baseline questionnaire EQ-5D-5 L® Index, at 1, 6 or 12 months after the surgery.

The secondary endpoint measures are:Differences between intervention groups greater than or equal to 10 point-change from the baseline questionnaire EQ-5D-5 L® utilities such as VAS, SI and HI at 1, 6 or 12 months post-surgery.Early postoperative combined endpoint of four major adverse complications (MAC) at 1 month (safety endpoint), including all-cause mortality, acute myocardial infarction, stroke or transient ischaemic accident, and classification of acute renal failure by Acute Kidney Injury Network (AKIN) greater than or equal to 2. Follow up at 1 year post-surgery.Severe nosocomial infections (pneumonia, early endocarditis, mediastinitis, sepsis).Need for rehospitalisation.Differences between interventions groups greater than or equal to 10 points change from the baseline SATISCORE® questionnaire at 1 and 6 months post-surgery.Postoperative hospital length of stay.Postoperative intensive care unit length of stay.Times for ischaemia and cardiopulmonary bypass (CPB).Mechanical ventilator support after surgery (intubation times).Bleeding in the first 24 h after surgery and transfusion requirements in the first 72 h.New York Heart Association (NYHA) functional class at 1 to 6–12 months.Survival at 12 months.

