Multivariate regression analysis techniques will be applied to control possible bias in effect caused by the patient’s initial situation (comorbidities). Pearson’s correlation test will be performed on EQ-5D-5 L® and SATISCORE® data. Survival analysis will be conducted using Mantel Cox log-rank analysis with the corresponding Kaplan-Meier survival chart.

The “intention to treat” population is defined to include all randomised subjects. This population will be used for endpoint analyses. The as-treated population (“per protocol”) is defined to include all subjects undergoing the index procedure. This population will be used for the analysis of adverse events.

Differences between MS and FS group scores at each follow-up time point will be estimated with longitudinal random-effect growth curve models, which will be fit to the repeated measurements for each health status outcome. These longitudinal analyses will use all available quality-of-life data: including data from patients who will subsequently die, withdraw, or will be lost to follow up. They will also accommodate missing data under the missing at random assumption. Variables that will be included in the models are: treatment assignment, pre-specified patient characteristics (age, sex, EuroScore), follow-up time and interactions between treatment and time. These models will be used to calculate the mean between-group differences in the EQ-5D index score and the individual subscales at each follow-up time point, and the associated 95% CIs and *P* values.

To examine the potential impact of missing data, which, given the illness severity of the trial population, would most likely not be missing at random, we will repeat the growth curve analyses after imputing the missing scores among the surviving patients, as the lowest reported score among respondents within each treatment group for each respective time point. We also will examine the magnitude of potential survivor bias by comparing the mean baseline scores between treatment groups for the subgroups of patients with available QOL data at each successive follow-up time point.

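### The only analysis that departs from missing at random fills survivors' gaps with the lowest score in their own arm, which adds chance noise and does not test whether a treatment difference is robust.

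*Protocol article*

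**What the plan says.** All of this is in the Statistical analysis section of the protocol article. The longitudinal growth curve models use all available data, "including data from patients who will subsequently die, withdraw, or will be lost to follow up". Of these models the plan says: "They will also accommodate missing data under the missing at random assumption".

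The plan then doubts that assumption. Missing data, "given the illness severity of the trial population, would most likely not be missing at random". In response, "we will repeat the growth curve analyses after imputing the missing scores among the surviving patients", each gap being filled "as the lowest reported score among respondents within each treatment group for each respective time point".

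A further check is descriptive: "We also will examine the magnitude of potential survivor bias by comparing the mean baseline scores between treatment groups", restricted at each visit to patients who have data. It adjusts nothing and sets no alternative assumption about the missing values. The lowest-score rule is therefore the only quality-of-life analysis that departs from missing at random.

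**The concern.** A sensitivity analysis for data not missing at random should vary the assumption about the unseen values in a controlled way and show when the conclusion changes. This rule falls short in four respects.

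- **It rests on one patient.** The imputed value is a sample minimum, taken separately in each arm and at each visit. A single low respondent fixes the value for every non-responding survivor in that arm. When the arms do not truly differ, any gap between the two minima is chance.
- **It ignores imputation uncertainty.** Each gap receives a constant that is then analysed as if it had been measured.
- **It does not stress the result.** Each arm's minimum moves with that arm's distribution. If ministernotomy shifts all scores up by 0.10, its minimum rises by 0.10 too, and with equal missingness the estimated difference stays put.
- **It is tied to the numerically lowest score.** The growth curve models are to be fitted for each health status outcome. On the Severity Index (Quality of life and satisfaction questionnaires) 0 means no health problems, so there the rule would impute the best health.

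At stake is whether the trial can say anything useful about the mechanism its own plan considers most likely.

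**Working it through.** **Inputs from the protocol article.** Target difference 0.10, SD 0.15, two-sided alpha 0.05, power 90%, 48 per arm needed and 100 randomised (Sample size calculation). The index runs from 1 down to −0.654 (Quality of life and satisfaction questionnaires).

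**The plan's own figure.** n per arm = 2 × (1.960 + 1.282)² × 0.15² / 0.10² = 47.3, rounded up to 48. This reproduces the stated size. The loss allowance is 100 − 96 = 4 patients, about 2 of 50 per arm (4%).

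**Assumptions not in the documents.** Mean score 0.80; left-skewed scores (1 minus a gamma variable) or normal scores, both with SD 0.15; 2 to 10 of 50 missing per arm, all survivors and missing at random; one visit, with a t test in place of the growth curve model.

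**Step 1: arithmetic of the shift.** With equal missingness,

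shift in arm difference = (missing share) × (gap between the two arm minima).

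- 2 of 50, largest possible gap: 0.04 × (1 + 0.654) = 0.066.
- 2 of 50, minima −0.654 and 0.3 (assumed): 0.04 × 0.954 = 0.038.
- 5 of 50, same minima: 0.10 × 0.954 = 0.095.
- 10 of 50, same minima: 0.20 × 0.954 = 0.191.

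**Step 2: how large the gap is by chance.** In simulated trials with no true difference and skewed scores, the gap between arm minima has a median of about 0.13 to 0.14 and a 90th percentile of about 0.366. The 90th percentile of the shift is then 0.04 × 0.366 = 0.015 at 2 of 50 and 0.10 × 0.366 = 0.037 at 5 of 50. With normal scores the median gap is about half as large (0.065).

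**Step 3: effect on the estimate and the test, no true difference.**

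| Missing per arm | SD of difference, observed data only (skewed) | SD of difference after the rule (skewed) | Type I error (skewed) | Type I error (normal) |
|---|---|---|---|---|
| 2 of 50 | 0.031 | 0.035 | about 4% | 4.0% |
| 5 of 50 | 0.032 | 0.044 | 5.6% | 3.7% |
| 8 of 50 | not tabulated | not tabulated | about 9% | 4.1% |
| 10 of 50 | 0.034 | 0.064 | about 13% | 5.7% |

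**Step 4: does the rule stress a true effect?** With a true difference of 0.10, skewed scores and equal missingness, the mean estimate after the rule is 0.100, 0.100 and 0.099 at 2, 5 and 10 missing per arm. The share of trials significant at 0.05 falls from 89% to 81%, from 88% to 68% and from 84% to 58%, compared with the observed data alone. The estimate is not challenged; it only becomes noisier.

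**Step 5: direction of the scale.** Severity Index = (sum of the five levels − 5) × 5. State 11111 gives (5 − 5) × 5 = 0, the best health. State 55555 gives (25 − 5) × 5 = 100, the worst. The lowest reported Severity Index is therefore the healthiest respondent's score.

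**The case against.** The strongest reply is that this is a secondary check beside a main model that assumes missing at random, and that the planned loss is small. About 2 of 50 per arm is allowed for, questionnaires can be completed by telephone, and additional recruitment is foreseen for patients who do not complete follow-up. At that loss even the most extreme pair of minima moves the difference by 0.066, less than the 0.10 target, and the type I error is about 4%. The inflation at higher loss needs skewed scores; neither the skew nor the mean of 0.80 is in the documents. All of this stands, and it limits the size of the point. It does not answer the design fault: at any loss rate, the check leaves the treatment difference untested against the mechanism the plan expects.

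A reader might infer two stronger things that the documents do not support.

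- **That the worst outcome is never counted, because deaths are not imputed.** The Study endpoints section puts mortality in the 1-month safety composite, "including all-cause mortality, acute myocardial infarction, stroke or transient ischaemic accident" among its components, and lists 12-month survival, which the Statistical analysis section tests by log-rank. Scores recorded before death also stay in the growth curve models. What is true is narrower: no quality-of-life analysis scores death. Describing quality of life among survivors and reporting mortality separately is a legitimate choice. With death scored 0 and an assumed survivor mean of 0.80, each excess death in an arm of 50 would move the difference by 0.80 / 50 = 0.016, so about six would be needed to reach 0.10.
- **That the check is likely to reverse the trial's conclusion.** In the skewed simulation a shift of 0.10 or more occurred in 0.07% of trials at 5 missing per arm and 1.2% at 8. Nor does the error rate of a sensitivity analysis decide the trial.

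**Conclusion.** The point holds as a weakness in the choice of sensitivity analysis. The only analysis aimed at data not missing at random depends on one respondent per arm and visit, treats imputed constants as data, and with equal missingness leaves a true difference where it was.

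Its numerical effect is small at the planned loss. It becomes material from roughly 10% missing upwards if scores are left-skewed: a 90th percentile shift of 0.037 at 5 of 50, over a third of the 0.10 target, and a type I error of about 9% at 8 of 50 and 13% at 10 of 50. With normal scores there is no material inflation. These figures rest on the assumed mean, shape and missing counts, and on a single-visit comparison.

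The Severity Index problem is conditional: it arises if the rule is applied to that scale as worded. The main model and the sample size are not affected.

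**What to change.** Replace the within-arm minimum with multiple imputation followed by a shift (delta) of the imputed scores towards worse health:

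1. Apply the same delta in both arms and increase it in steps until the conclusion changes (the tipping point).
2. Repeat with the delta in one arm only, for each arm in turn. This variant is needed: the change in the arm difference is the difference between the arms' values of (missing share × delta), so with equal missingness a common delta cancels. A one-arm delta of 0.30 (illustrative) with 5 of 50 missing moves the difference by 0.10 × 0.30 = 0.03.
3. Define worse health for each scale: downward for the EQ-5D index, visual analogue scale, Health Index and SATISCORE, upward for the Severity Index.

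This removes the dependence on one respondent, carries imputation uncertainty into the intervals and shows how pessimistic one must be before the result fails. The cost is modest programming and a longer sensitivity table; no new data and no change in sample size are needed.

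A supplementary analysis that scores the EQ-5D index as 0 from death onward is optional and not required. It would answer a different question and has no counterpart for SATISCORE.

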### Dissemination

Trial results will be posted on ClinicalTrials.gov, published in peer-reviewed journals, and presented at national conferences. Data-sharing policy will be under request to the Sponsor and publicly explained and recorded at ClinicalTrials.gov.

### Limitations of the study

Among this study’s limitations, there could be some confusion bias introduced by variables, which will be controlled in the statistical analysis using multivariate linear regression analysis. The absence of masking the surgeon may introduce an unmeasurable bias into the study. The sample size is not designed to detect differences in mortality, although a combined safety endpoint such as this one may help to find differences between groups. The use of general QOL questionnaires such as EQ-5D-5 L means that the outcome does not depend exclusively on the surgical technique employed, but also on other diseases and/or complaints that the patient has previously or that may be acquired in the future, independently of the heart condition. The size of the sample could also be insufficient if the standard deviations are shown to be higher than those presented in previous research.

## Summary and trial status

The QUALITY-AVR trial (NCT02726087) aims to test the hypothesis that MS improves QOL, satisfaction and clinical outcomes in patients referred for isolated AVR. The design of this study is unique to date, as there is no randomised clinical trial to have compared these outcomes. We hope that the results of the study can influence the future of AVR surgery and encourage the adoption of a new surgical “gold standard” for MS, with improved QOL and outcomes, in the short and long term. If this proves to be the case, clinical trials comparing TAVI to surgery should include MS to evaluate outcomes in low and intermediate risk patients as the “control” group. Recruitment began in March 2016 (75 patients currently recruited at November 2017) and it is expected to end in May 2018. All outcomes will be published within 2 years in accordance with Consolidated Standards on Reporting Trials (CONSORT) recommendations.

## Abbreviations

AKIN: Acute Kidney Injury Network
AVR: Aortic valve replacement
CBP: Cardiopulmonary bypass
EQ-5D-5 L: EuroQOL Quality of life Questionnaire 5 dimensions 5 Levels
FS: Full sternotomy (conventional surgery)
HI: Health Index
MAC: Major adverse complications
MS: Mini sternotomy
QOL: Quality of life
SI: Severity Index
*TAVI*: Transcatheter aortic valve implantation
VAS: Visual analogue scale
